### Sample size

We used data from a recent meta-analysis,^19^ which reported that 39% of women were anaemic at 6 weeks postpartum, as the control event rate. A sample size of 697 participants per group would provide 90% power to detect a relative reduction of 20% for intravenous iron to reduce the event rate of anaemia at 6 weeks postpartum to 30%, after accounting for 10% loss to follow-up. Power calculations assume a 1:1 randomisation ratio to each of the two treatment arms. 1400 women will be enrolled into the trial.

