### Statistical methods and analysis

Primary analyses will be conducted with the intention to treat principle. Categorical variables will be expressed as frequencies and percentages. Continuous variables will be presented as means (SD) or medians (interquartile ranges) depending on whether they are normally distributed or not. The effect of intravenous iron (vs oral iron) on the primary endpoint will be analysed using log-binomial regression models to obtain relative risks, 95% CIs and p values. The impact of clustering by site will be evaluated by comparing to logistic generalised linear mixed models using likelihood ratio tests, and the more parsimonious model presented. The extent to which inclusion of baseline covariates modifies the precision of estimates will be explored. Generalised linear mixed models will be used to estimate the effect of the treatment arm on repeated measures of haemoglobin and iron status biomarkers. The proportion of participants who are anaemic or iron deficient, and the proportion of participants who achieve anaemia correction at 6 weeks and 6 months follow-up will be compared. Subgroup analyses will be conducted to compare study findings by region (Lagos, Kwara, Kano and Rivers), mode of birth (caesarean vs vaginal birth) and by the occurrence of primary postpartum haemorrhage. A two-tailed test of hypothesis will be performed based on an alpha level of 0.05. R and RStudio (2020)http://www.rstudio.com/ will be used for statistical analysis.^20^ An interim analysis will be conducted by an independent statistician after achieving 50% of the sample size and data presented to the Data Safety and Monitoring Board (DSMB). Based on O’Brien-Fleming method,^21^ the threshold for significance of the primary endpoint at the interim analysis will be alpha=0.0054. The clinical trial will be terminated if the null hypothesis is rejected. The alpha level for the analysis at the end of the study will be adjusted to 0.0492 based on alpha adjustment based on O’Brien-Fleming method.

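### The stated O'Brien-Fleming levels (0.0054 interim, 0.0492 final) give an overall two-sided type I error of about 0.0513 at 50% information, slightly above the stated 0.05

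*Protocol article*

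**What the plan says.** All the elements of the group-sequential rule are in one paragraph of the protocol article, Statistical methods and analysis:

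- Overall level: "A two-tailed test of hypothesis will be performed based on an alpha level of 0.05".
- Timing: "An interim analysis will be conducted by an independent statistician after achieving 50% of the sample size". With 1400 women planned (Sample size), this is 700 women.
- Interim level: "the threshold for significance of the primary endpoint at the interim analysis will be alpha=0.0054".
- Action at the interim: "The clinical trial will be terminated if the null hypothesis is rejected".
- Final level: "The alpha level for the analysis at the end of the study will be adjusted to 0.0492", which the text says is "based on alpha adjustment based on O’Brien-Fleming method".

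The number of looks, the timing, the named method and both thresholds are therefore all stated. The check below needs nothing from an analysis plan.

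**The concern.** Stopping for efficacy at the interim uses up part of the 5% error, so the final level has to be lowered enough to pay for it. Lowering it from 0.05 to 0.0492 gives back only 0.0008, which looks too little after an interim test at 0.0054 with half the data. The two levels are the only decision thresholds given for the primary endpoint. If they do not combine to 0.05, the primary test does not have exactly the error rate the plan states, and a final p-value just under 0.0492 would be called significant when a boundary calibrated to 0.05 would not reject.

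**Working it through.** **Inputs** (all from Statistical methods and analysis): two-sided overall level 0.05; two looks; information fraction t = 0.5; interim level 0.0054; final level 0.0492; efficacy stop at the interim.

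**Step 1. Convert levels to critical values.** For a two-sided level a, c is the standard normal quantile at 1 − a/2.
- 0.0054 gives c1 = 2.782.
- 0.0492 gives c2 = 1.967.
- c1/c2 = 1.4145, practically √2. This is the classical O'Brien-Fleming shape for two equally spaced looks, with constant 1.967.

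**Step 2. Overall error of the stated pair.** Under the null hypothesis Z1 and Z2 are standard normal with correlation √t = √0.5 = 0.7071.

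Overall error = 1 − P(|Z1| < 2.782 and |Z2| < 1.967) = 0.0513 by numerical integration (0.05129). A simulation of 20 million trials gave 0.0513.

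Of this, 0.0054 is spent at the interim and 0.0513 − 0.0054 = 0.0459 is added by the final test. To total 0.05, the final test may add only 0.05 − 0.0054 = 0.0446.

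**Step 3. Can rounding or another reading explain it?**
- Both levels at their lower or upper rounding limits (0.00535 and 0.04915; 0.00545 and 0.04925): 0.0512 and 0.0514.
- Both levels read as one-sided: 0.0509 against 0.05.
- O'Brien-Fleming-type alpha spending at t = 0.5: 0.0031 and 0.0490 when 0.025 is spent per tail; 0.0056 and 0.0478 when two-sided 0.05 is spent. Neither is the stated pair.

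**Step 4. Levels that do hold 0.05 at t = 0.5.**
- Classical form: solve P(|Z1| > c√2 or |Z2| > c) = 0.05. This gives c = 1.977 and c√2 = 2.797, that is 0.0480 final and 0.0052 interim.
- Interim kept at 0.0054: the final level must be 0.0479.
- Final kept at 0.0492: the interim level can be at most about 0.0026.

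**Step 5. Dependence on timing of the interim, stated pair.**

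| Information fraction | Overall two-sided error |
|---|---|
| 0.40 | 0.0520 |
| 0.45 | 0.0516 |
| 0.50 | 0.0513 |
| 0.55 | 0.0510 |
| 0.60 | 0.0506 |
| 0.70 | 0.0500 |
| 0.75 | 0.0497 |

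The crossing is at 0.703; beyond it the pair is slightly conservative.

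**Step 6. Power cost of correcting.** Sample size gives 697 per arm with 10% loss: 697 × 0.9 = 627 evaluable. With 39% versus 30%, the expected final Z is 0.09 / √[(0.39 × 0.61 + 0.30 × 0.70)/627] = 0.09 / 0.02673 = 3.367. Two-look power is 0.9202 with the stated pair and 0.9186 with 0.0052 and 0.0480, a loss of 0.0016. With 0.0054 and 0.0479 it is 0.9185.

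**The case against.** **The excess is tiny.** An error of 5.13% instead of 5% rounds to the 0.05 that the plan states. This stands as a limit on severity. It does not make the pair correct, because the levels are given to four decimals as the outcome of an adjustment meant to hold 0.05.

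**The planned test is itself approximate.** The primary model is log-binomial regression on binary data, and 0.0513 is a large-sample figure. Simulating an unadjusted two-arm log-binomial Wald test at a 39% event rate gives about 0.050 for the stated pair and about 0.049 for 0.0052 and 0.0480. Over event rates from 30% to 48% the ranges are about 0.050 to 0.053 and about 0.047 to 0.051. So discreteness can move the actual rate by as much as the defect. That stands as a reason not to read 0.0513 as this trial's exact error rate. But these boundaries are defined by the large-sample theory, and under it the pair misses.

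**The levels may come from the cited source.** The √2 ratio suggests that a single constant was used deliberately. A reader might infer that the authors misapplied the reference they cite. The document does not support that, since the reference is not shown. Only the probability can be checked, and it does not depend on where the constant came from.

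**The 95% confidence intervals.** A reader might infer a contradiction between 95% intervals and a final test at 0.0492. The plan lists the intervals as estimation output and decides significance by the stated levels, so whether to report a matching interval is a reporting preference and not part of this error.

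**Conclusion.** Wrong as written, and minor. At 50% information the stated pair gives an overall two-sided type I error of about 0.0513, an excess of 0.0013 over 0.05. The larger discrepancy is in the final level (0.0492 against 0.0479 to 0.0480); the interim level is close to the classical 0.0052. The decision could change only for a final p-value between about 0.048 and 0.0492.

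This rests on three assumptions: large-sample normal test statistics; half the sample size meaning half the statistical information on the primary outcome; and the interim stopping rule being followed. An earlier look in information terms makes the excess larger (0.0520 at 40%); a look at about 70% or later removes it.

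A reader might infer that the trial's primary claim is unsafe or that its error rate is materially inflated. The figures do not support that: the excess is about a fortieth of the nominal level (0.0013/0.05 = 0.026).

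**What to change.** Before the final analysis, correct the levels in the protocol and the analysis plan:

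1. If the interim was or will be tested at 0.0054, set the final level to 0.0479 (|z| of at least 1.978). This case is the more likely one. Trial status gives first enrolment on 7 December 2022 and a projected end of recruitment by June 2024, and the article appeared in August 2024. The document does not say whether the look has taken place.
2. If the interim has not yet taken place, use 0.0052 (|z| of at least 2.797) at the interim and 0.0480 (|z| of at least 1.977) at the end.

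Both options assume the look is at 50% information. If it took place at a different fraction, recalculate the final level for that fraction.

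The cost is one or two numbers in the text and about 0.16 points of power (92.0% to 91.9% at 39% versus 30% with 627 evaluable per arm). No further women, visits or data are needed.

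### The interim and final levels (0.0054 and 0.0492) have the O'Brien-Fleming shape but a slightly low constant, so the overall two-sided type I error is about 5.13% rather than 5%

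*Protocol article*

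**What the plan says.** All the statements are in the protocol article, under Statistical methods and analysis.

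- General level: "A two-tailed test of hypothesis will be performed based on an alpha level of 0.05".
- Timing of the look: "An interim analysis will be conducted by an independent statistician after achieving 50% of the sample size".
- Interim level: "the threshold for significance of the primary endpoint at the interim analysis will be alpha=0.0054".
- Consequence of crossing it: "The clinical trial will be terminated if the null hypothesis is rejected".
- Final level: "The alpha level for the analysis at the end of the study will be adjusted to 0.0492", described as "based on alpha adjustment based on O’Brien-Fleming method".

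The Sample size section gives the total: "1400 women will be enrolled into the trial". The article does not write out an overall error rate across the two looks. A target of 5% is the natural inference from the general level and from the fact that the final level is described as adjusted.

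**The concern.** A final level is lowered after an interim efficacy look for one reason: to keep the chance of a false positive over both looks at the stated alpha. The level of 0.0492 looks high for a two-look O'Brien-Fleming design that spends 0.0054 at half the information. If the pair overspends, a final p value just below 0.0492 would be declared significant on the primary endpoint although a design that holds 5% would not reject. These are printed decision thresholds, so the point does not depend on detail that may be left to a statistical analysis plan.

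**Working it through.** **Inputs** (Statistical methods and analysis): two-sided alpha 0.05; one interim plus the final; interim level 0.0054; final level 0.0492; stop on rejection at the interim. Information fraction t = 0.5, from the look at 50% of the sample size. The "Power calculations assume a 1:1 randomisation ratio to each of the two treatment arms" statement in Sample size does not enter the alpha calculation.

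**Step 1: the plan's levels as z values.** z = Φ⁻¹(1 − p/2).
- Interim: p = 0.0054 gives 2.782.
- Final: p = 0.0492 gives 1.967.
- Ratio: 2.78215 / 1.96685 = 1.4145.

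An O'Brien-Fleming boundary with two equally spaced looks has c₁ = √2 × c₂, and √2 = 1.4142. Starting from 0.0492 and applying that relation gives an interim level of 0.00541. The plan's pair is therefore reproduced as an O'Brien-Fleming shape with constant 1.967.

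**Step 2: the overall error of that pair.** Under the null, the interim and final z statistics are bivariate normal with correlation √t = √0.5 = 0.707.

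Overall error = 1 − P(|Z₁| < 2.782 and |Z₂| < 1.967) = **0.0513**

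Numerical integration gives 0.05129, and a simulation of 20 million draws gives 0.0513. Moving both levels within their rounding (0.00535 to 0.00545 and 0.04915 to 0.04925) gives 0.0512 to 0.0514, so rounding does not explain the excess.

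**Step 3: the constant that gives 5%.** Solve 1 − P(|Z₁| < √2·C and |Z₂| < C) = 0.05. The result is C = 1.9774, so z = 2.797 and 1.977, with nominal levels 0.0052 and 0.0480. Put back with rounding, these two levels give 0.0500.

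**Step 4: can another construction give the printed pair at 5%?**

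| Construction at t = 0.5, overall 0.05 | Interim | Final |
|---|---|---|
| Printed in the article (overall 0.0513) | 0.0054 | 0.0492 |
| Exact O'Brien-Fleming | 0.0052 | 0.0480 |
| O'Brien-Fleming-type spending, 0.025 per side | 0.0031 | 0.0490 |
| O'Brien-Fleming-type spending, two-sided 0.05 | 0.0056 | 0.0478 |
| Interim kept at 0.0054 | 0.0054 | 0.0479 |
| Final kept at 0.0492 | 0.0026 | 0.0492 |

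None of the constructions that hold 5% gives 0.0054 with 0.0492.

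**Step 5: sensitivity to the information fraction.** The printed levels give the following.

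| t | Overall error | Final level needed after 0.0054 |
|---|---|---|
| 0.40 | 5.20% | 0.0472 |
| 0.43 | 5.18% | 0.0474 |
| 0.50 | 5.13% | 0.0479 |
| 0.556 | 5.09% | 0.0483 |
| 0.60 | 5.06% | 0.0485 |
| 0.70 | 5.00% | 0.0492 |

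Two rows correspond to readings of the trigger, both with 1400 × 0.9 = 1260 evaluable women (10% loss, from Sample size).
- 700 women enrolled: the first enrolment on 7 December 2022 and recruitment assumed to end on 30 June 2024 (Trial status gives only June 2024) span 571 days. With uniform accrual, 1400/571 × 42 = 103 women would still be short of 6 weeks. Then (700 − 103) × 0.9 = 537, and 537/1260 ≈ 0.43.
- 700 women with outcomes: 700/1260 = 0.556.

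**Step 6: power cost.** Take a true effect for which a single 5% test has 90% power. With t = 0.5, the printed pair has power 0.8999 and the 0.0052/0.0480 pair has 0.8980, a loss of about 0.2 percentage points.

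**The case against.** The strongest reply is that very little is at stake. The excess is 0.13 percentage points, the affected band of final p values is 0.12 points wide, and the design, sample size and effect estimate do not change. That is right, and it sets the severity. It does not make the printed numbers correct for 5%.

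Three stronger readings are tempting, and the article does not support them.

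- A reader might infer that the levels are not O'Brien-Fleming levels at all. The z ratio shows otherwise: the shape is right and only the constant is low. The article cites a source for the method that is not at hand, so it cannot be said whether the constant was tabulated there or mistaken in transfer.
- A reader might infer that the look falls well before half the information, which would worsen the excess. The article does not say whether half the sample size means women enrolled or women with outcomes. The enrolment reading gives 5.18% under assumed uniform accrual and an immediate data cut; the outcome reading gives 5.09%. A later look shrinks the excess further. The exact data-cut rule may also properly sit in a document that is not shown.
- A reader might infer that the general 0.05 conflicts with the adjusted level. It does not, because the article gives the primary endpoint its own interim threshold and an adjusted final level.

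It is also fair to say that the article never states an overall 5% in words. That target is inferred, but no other purpose for adjusting the final level is evident.

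**Conclusion.** Minor, and wrong as written. The printed pair has the O'Brien-Fleming form with a constant of 1.967 instead of 1.977, and it gives an overall two-sided type I error of about 5.13% where 5% is implied. At the final analysis it changes the conclusion only for a p value between about 0.048 and 0.0492; the matching strip at the interim, 0.0052 to 0.0054, is narrower still. The figure assumes an interim at exactly half the information and the usual bivariate normal approximation. Across fractions from 0.40 to 0.60 it stays between 5.20% and 5.06%, and it reaches 5.00% only near 0.70. This does not threaten the validity of the trial.

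**What to change.** Replace the two levels with 0.0052 at the interim and 0.0480 at the end. A change to a spending function is not needed to correct the error.

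If the interim has already been carried out at 0.0054, leave that look as it was and set the final level from the actual information fraction at the time, counting information as women with a 6-week haemoglobin outcome: 0.0479 at one half, about 0.0474 at 0.43. Make the change before the final unblinded analysis, since a threshold altered afterwards would not be credible.

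The cost is two numbers, or one number and a clause, and about 0.2 percentage points of power. No change to the sample size is needed on this account.

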### Data monitoring

The day-to-day management of the trial is the responsibility of the Trial Management Group (TMG) who ensure high-quality delivery of the trial in accordance with agreed timelines, including early identification of potential problems and mitigations. The TMG reports to the independent TSC who are responsible for oversight of the trial. The TMG includes the chief investigator, co-investigators, the trial manager and data manager. The independent DSMB meets at regular intervals throughout the trial; they aim to protect the trial’s validity and credibility. The DSMB are responsible for monitoring the trial data and they report to the TSC. The committee members met before the commencement of the study and they are to meet at least annually to review unblinded data, monitor the progress of the study, recruitment rate and to assess whether there are any significant safety concerns or ethical issues. If they find any, they make recommendations to the TSC regarding whether the trial should be halted, modified or continued as planned. The TSC reviews them carefully and consider the recommendations alongside other aspects of the trial’s progress. Based on this review, the TSC may decide to implement the recommendations, modify the trial protocols or take other appropriate actions to address any identified concerns. They monitor the progress of the trial by holding virtual meetings two times a year or as the need arises.

The clinical monitors conduct routine monitoring online and onsite every 2 weeks to ensure reported trial data are accurate, complete and verifiable from source documents, and that the conduct of the trial follows the currently approved protocol/amendment(s), with Good Clinical Practice, and applicable regulatory requirement(s).

Auditing of research records will be done by the monitoring committees as outlined above, while financial auditing will be done by the Research Management Office and Audit Department of University of Lagos.

### Implementation study

The Consolidated Framework for Implementation Research (CFIR)^22^ and RE-AIM framework^23^ will guide our implementation research approach. The CFIR is a determinant framework made of five domains and multiple constructs. These domains are intervention characteristics, outer setting, inner setting, individuals’ characteristics and implementation process. Specifically related to our study, we identified some constructs of each domain that will facilitate the understanding of implementing FCM in our setting (figure 4). The CFIR will be used to guide and structure our implementation research approach.

**Figure 4 F4:**
[figure not shown]
Implementation evaluation guided by the Consolidated Framework for Implementation Research.

### Data collection methods

To evaluate the outcome measures, qualitative and quantitative data will be collected. We will qualitatively evaluate the acceptability and feasibility of FCM using semistructured interview guides that are developed by CFIR. Specifically, we will conduct focus group discussions (FGDs) and key informant interviews (KIIs) among stakeholders of interest in each state prior to and after the trial’s commencement. Following the trial, stakeholders will be informed of the preliminary findings prior to the FGDs and KIIs. The stakeholders are general postpartum women with and without anaemia, postpartum women with past or current anaemia treatment, partners of postpartum women, healthcare personnel (HCPs) (eg, doctors, nurses, pharmacists, laboratory technologists, community health officers etc), health facility managers, community leaders and policymakers. The aim of the baseline assessment is to prospectively identify contextual barriers and facilitators to the trial implementation, while the endline will evaluate barriers and facilitators towards post-trial adoption, scale-up and sustainability. The sampling of respondents will be purposive but cut across various categories of stakeholders in the three levels of the health system in the various states.

FGDs were chosen as they enable members within stakeholder groups to interact, resulting in a comprehensive description of stakeholders’ perceptions of implementation outcomes.^23^ KIIs provide an opportunity for in-depth one-on-one discussions and are more practical to arrange for the identified stakeholders.^24^ We aim to conduct 48 KIIs and 12 FGDs, or until data saturation has been reached (a point in data collection when no additional issues or insights are identified from interviewing additional participants). Trained independent research assistants will conduct all interviews using purpose-designed interview guides specifically for each group of stakeholders. Verbal consent will be obtained from each participant before the start of every interview. Audio recordings will be made only with permission and transcribed verbatim.

Acceptability and feasibility will be assessed quantitatively using the Acceptability of Intervention Measure (AIM) and Feasibility of Intervention Measure (FIM) tools.^25^ These self-administered electronic survey tools will be completed through REDCap by HCPs administering FCM to postpartum women across all states, both before and after the trial.

Triangulation of the quantitative and qualitative findings will be conducted to provide a comprehensive understanding of the implementation outcomes. The quantitative data from the AIM and FIM tools will provide numerical measures of acceptability and feasibility, while the qualitative data from the FGDs and KIIs will offer in-depth insights into the contextual factors influencing these outcomes. By integrating the findings from both data sources, we can identify areas of convergence and divergence, enhancing the validity and reliability of the results. This triangulation approach will allow us to develop a more nuanced understanding of the barriers and facilitators to implementing FCM in the study setting, informing future adoption, scale-up and sustainability efforts.

